#### Brief symptom inventory (BSI; [37])

The BSI is a 53-item self-report questionnaire that administers a multidimensional complaint list that shows the extent to which a participant suffers from various psychological and physical symptoms. Each item is rated on a 4-point scale (0 = none at all to 4 = a lot) and are divided into nine subscales: somatic complaints, cognitive problems, interpersonal sensitivity, depressed mood, fear, hostility, phobic fear, paranoid thoughts, and psychoticism. A version has been translated to Dutch by de Beurs and Zitman [38].

#### Obsessive-compulsive inventory – revised (OCI-R short version; [17])

The OCI-R is a short version of the original OCI and is a self-report scale for assessing symptoms of Obsessive-Compulsive Disorder (OCD). It contains 19 questions that the participant answers using a 5-point Likert scale. The item scores are added up and the possible range of scores is between 0 and 72. Scores 21 or above indicate the likely presence of OCD. A version has been translated to Dutch by Cordova-Middelbrink, Dek and Engelbarts [39].

#### Ruminative response scale (RRS; [15])

The RRS is a self-report measure that assesses ruminative responses to depressed mood. It is a revision of the original longer Response Styles Questionnaire. It consists of 22 items and measures two aspects of rumination: brooding and reflective pondering. Each item is rated on a 4-point scale (1 = almost never to 4 = almost always), and the possible range of scores is between 22 and 88. The Dutch translation of the scale has been found to be internally consistent (a = .90; [40]).

#### Beck hopelessness scale (BHS; [41])

The BHS is a widely used standardized measure of hopelessness. The BHS consists of 20 ‘true-false’ statements covering positive and negative thoughts about the true-false response. The item scores are added up and the possible range of scores is between 0 and 20. The predictive validity of the BHS for suicide and attempted suicide was supported by the authors of the scale [42], and was confirmed by later research [43, 44]. The Dutch translation of the scale has been found to be internally consistent (a = 0.68–0.75; [45]).

#### Childhood trauma questionnaire-short form (CTQ-SF; [16])

The CTQ-SF is a 28-item retrospective self-report questionnaire that is designed to assess five types of negative childhood experiences: emotional neglect, emotional abuse, physical neglect, physical abuse, and sexual abuse. The tendencies to minimize or deny abuse experiences are measured as well. The truth of each statement is rated on a 5-point scale. The CTQ-SF has adequate reliability and validity [16].

#### N-back task [46]

The N-back task is used to measure executive functioning. Patients are asked if the letter on the screen matches a letter previously (0 (baseline), 1, 2, or 3 back) presented. Only when the patient performs well on the 2-back, will he or she be forwarded to the 3-back part of the task. Working memory load increases as the task progresses from 1-back to 3-back and is suggested to require executive processes. The task will take around 15 min and the accuracy of responses and reaction times will be measured.

#### Breathing focus task (BFT; [19])

The BFT is a measure of the behavioural state related to intrusive thoughts. It consists of 5 min of focus on breathing, where patients are asked 12 times about their current thoughts. Patients briefly describe the current thought in keywords and indicate the emotionality (positive, neutral, negative). After the 5-min breathing focus phase, each of the none-breathing answers (so each intrusion) is discussed with the patient to get more insight on the nature of the thought.

#### Prospective imagery task (PIT; [47, 48])

Participants are asked to form a mental image of 10 negative future scenarios and 10 positive future scenarios. These include events such as: ‘you will have a serious disagreement with your friend’ or ‘you will do well on your course’. Images are rated on vividness on a 5-point Likert scale (ranging from 1 = no image at all to 5 = very vivid). The PIT has good internal consistency [47]. This task can and will be administered as a questionnaire.

#### Response to intrusions questionnaire – negative appraisal subscale (RIQ; [18, 49])

Participants are asked about a negative memory they experienced in the past week. Six items assessing negative appraisals of intrusions are rated on a 7-point Likert scale (ranging from 1 = totally disagree to 7 = totally agree). This subscale is reported to have good internal consistency (a = 0.84; [49])*.*

#### EMDT treatment measures

Various aspects of the intervention preceding and following the EMDT sessions will be administered. Participants will answer six questions about their expectations of the treatment (e.g. thoughts and feelings about the efficacy of the treatment and expectations about recovery). These questions will be answered before being randomized. EMDT-treatment compliance will be operationalized as the amount of no-shows (not showing up without notifying the EMDT therapist), cancelled and replaced appointments. Patients in the intervention group will answer 19 items evaluating the EMDT add-on sessions. Patients are asked to rate aspects of the treatment on a ten-point scale (ranging from 0 = not good at all to 10 = very good) and provide feedback and possible suggestions. An explanation is asked (5 items) why the patient thinks his or her symptoms did (not) improve.

#### Treatment integrity

In order to measure therapist adherence to the EMDT treatment protocol, independent raters will review a random selection of videotaped EMDT sessions. For the purpose of this study, we have developed an EMDT-session Checklist that describes the essential parts of each session. The independent raters will use this 12-item dichotomous yes/no checklist, to check therapist adherence to the treatment condition.

### Data analyses

Data-analyses will include intention-to-treat analysis and additional subgroup analyses. Missing data will be imputed using multiple imputation. The reduction in frequency of intrusive suicidal imagery is analyzed using hierarchical linear modeling. Between-group scores on secondary measures (like BDI, SIDAS, BSSI, RRS, and BHS) will also be compared using hierarchical linear modeling.

Latent difference score (LDS) models are used to examine any potential mediation effects of suicidal imagery on suicidal ideation, depression, and hopelessness. LDS models will also be used to investigate a potential underlying mechanism of the intervention itself using the pre- and post-treatment scores on the n-back task. Moderators may play a direct role in elaborating mediators and mechanisms of change [50, 51], thus we are looking at potential (moderated) mediation effects using potential moderating variables such as childhood trauma, rumination, and obsessive-compulsive traits. To examine potential mechanisms of change, both multilevel models and structural equation models (SEM) will be used.

#### Cost-effectiveness analyses

To analyze the cost-effectiveness of the EMDT add-on treatment, societal costs will be measured using the TiC-P at baseline and after 3, 6, 9, and 12 months. Direct societal costs entail primary and secondary care, complementary and home care. Indirect costs entail absenteeism from paid and unpaid work, and presenteeism. The latter costs will be determined using a friction cost approach. Costs will be related to the following effect measures in the economic evaluation: the decrease in frequency and vividness of suicidal imagery as measured through the schematic overview in the appendix of the Intrusion Interview, and Quality-adjusted-life-years (QALYs) based on the Dutch tariff for the EuroQol (EQ-5D-5L).

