### Sample size

We cannot provide estimates on the reduction of suicidal intrusions as a result of the study, as we are not aware of similar interventions tested in this population and the outcome measure (Intrusion Interview; [6]) does not produce a standardized outcome. Therefore, we based our power analysis on the expectation of a medium to large effect size of 0.7 of TAU + EMDT as compared to TAU at 3 months on the primary outcome (suicidal intrusions). Power calculations suggest a minimum sample size of 38 participants per group (power = 0.85, alpha = 0.05, two-sided). Accounting for 15–20% attrition, we aim to include 45 participants per group. This adds to a total of 90 participants.

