### Procedure

The study will be carried out at various Dutch specialized mental healthcare centers including Arkin (Amsterdam), Altrecht (Utrecht), Dimence (Zwolle), GGZ Oost-Brabant (Oss, Boekel, Helmond, Boxmeer), GGZ Eindhoven, Parnassia Groep (The Hague), Pro Persona (Nijmegen), and the Vincent van Gogh Institute (Venray, Venlo). Each healthcare center will have its own contact person/research assistant, and patients will be recruited within the appropriate department.

After providing oral and written informed consent, patients will be screened for suicidal ideation (SIDAS), depressive symptoms (BDI-II) and DSM-IV diagnoses (M.I.N.I.). Next, the breathing focus task (BFT) is administered and participants are interviewed (using the Intrusion Interview) by trained staff members of the mental health care institution where they are currently being treated. They are asked to complete a set of (online) self-report instruments and answer the following screening questions: ‘do the suicidal intrusions hinder you in your daily life?’ and ‘do you feel tormented by these suicidal intrusions?’. If they answer yes on at least one of those statements, they are invited for the next appointment. During this appointment, they will provide oral and written informed consent and the schematic overview of the Intrusion Interview is administered. While at home, they are asked to fill in additional questionnaires and perform a computer task (n-back task). Next, the participant is randomized into the intervention group (EMDT + TAU) or the control group (TAU only). Participants in the experimental group will, in addition to their TAU, receive one introduction meeting with an EMDT-therapist, a maximum of six weekly EMDT add-on sessions, and six weekly online assessments (SIDAS, BDI-II). Participants in the control group will, in addition to their TAU, receive the same six weekly online assessments. Additional assessments will be carried out at: pre-treatment (baseline), during treatment, post-treatment (six weeks after baseline), and at 3, 6, 9 and 12 months follow-up.

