### Instruments

An overview of all patient instruments per assessment is given in Table 1. The duration of the (online) questionnaires range from 10 to 70 min.

**Table 1 Tab1:** Overview of patient instruments per time point

Instruments	S	B	T1	T2	T3	3	6	9	12
Suicidal Intrusions									
Intrusion Interview (II)		•	•		•	•	•	•	•
Response to Intrusions Questionnaire (RIQ)		•							
Suicidal Intrusions Attributes Scale (SINAS)		•			•	•	•	•	•
Suicidal Ideation									
Suicidal Ideation Attributes Scale (SIDAS)	•	•		•	•	•	•	•	•
Beck Scale for Suicidal Ideation (BSSI)		•			•	•	•	•	•
Depression									
Beck Depression Inventory (BDI-II)	•	•		•	•	•	•	•	•
Quality of life									•
EQ-5D-5L			•				•	•	•
Societal Costs									
Trimbos/iMTA questionnaire for Costs associated with Psychiatric Illness (TiC-P)			•			•			•
Psychological Problems									
Brief Symptom Inventory (BSI)		•			•	•			•
Rumination									
Ruminative Response Scale (RRS-NL)		•			•	•			•
Obsessive Compulsive Disorder									
Obsessive Compulsive Inventory – Revised (OCI-R)		•			•	•			•
Hopelessness									
Beck Hopelessness Scale (BHS)		•			•	•			•
Childhood trauma									
Childhood Trauma Questionnaire (CTQ-SF)		•							
Other measures									
M.I.N.I. Neuropsychiatric Interview	•								
Demographics Questionnaire		•							
N-back Task			•		•				
Breathing Focus Task (BFT)		•							
Prospective Imagery Task (PIT)		•							
Care-as-usual Treatment Details					•				
EMDT Treatment measures			•		•				

*S* Screening, *B* Baseline assessment, *T1* Pre-treatment assessment, *T2* During treatment, *T3* Post-treatment, *3* 3 month follow-up, *6* 6 month follow-up, *9* 9 month follow-up, *12* 12 month follow-up

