#### Trimbos/iMTA questionnaire for costs associated with psychiatric illness (TiC-P; [35])

The societal costs during this study will be measured using the TiC-P, which consists of two parts. The first part focuses on the use of (psychiatric) health care including primary and secondary care, complementary care and home care (4 items). The second part focuses on compromising costs due to loss of production including absenteeism from paid and unpaid work, and presenteeism (15 items). The valuation of health care utilization standard prices will be used [36], and medication use will be valued using prices of the Royal Dutch Society for Pharmacy (Z-Index, 2006).

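### The TiC-P cost questionnaire is scheduled at 6 and 9 months in the text but not in Table 1, so 12-month societal costs may be incomplete until the two are reconciled

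*Protocol article*

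**What the plan says.** The Cost-effectiveness analyses section gives five cost measurements: "societal costs will be measured using the TiC-P at baseline and after 3, 6, 9, and 12 months". One of the effect measures set against costs is "Quality-adjusted-life-years (QALYs) based on the Dutch tariff for the EuroQol (EQ-5D-5L"). That section names the EQ-5D-5L as the source of QALYs but gives no visit schedule for it.

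Table 1, under Instruments, has the header "Instruments S B T1 T2 T3 3 6 9 12". Its TiC-P row is marked at T1, 3 and 12 months. Its EQ-5D-5L row is marked at T1, 6, 9 and 12 months. The heading row directly above, "Quality of life", names no instrument but carries a mark under 12 months.

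The Procedure section lists the additional assessments as "pre-treatment (baseline), during treatment, post-treatment (six weeks after baseline), and at 3, 6, 9 and 12 months follow-up", so it treats pre-treatment and baseline as the same occasion.

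The TiC-P subsection says "The societal costs during this study will be measured using the TiC-P, which consists of two parts" and describes them as health care use and lost production. It states no recall period.

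**The concern.** Cost-effectiveness is the third stated aim of the trial, and a 12-month cost total needs the follow-up year to be covered. The text and Table 1 disagree on whether the TiC-P is given at 6 and 9 months. If Table 1 is the working schedule, costs in the middle of the year may never be reported, depending on how far back each form asks.

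The multiple imputation planned under Data analyses would help little with this. A form given to nobody at a visit leaves no observed values at that visit to impute from, so the gap would have to be filled by assumption.

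The EQ-5D-5L row raises a lesser question. As tabulated, utility is not measured at 3 months, and costs and utilities are taken together only at T1 and 12 months. The Study status section says that data are already being collected, so any form missing from the live schedule is lost for each participant who passes that visit.

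**Working it through.** **1. The two schedules side by side**

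| Source | T1 (baseline) | 3 | 6 | 9 | 12 |
|---|---|---|---|---|---|
| TiC-P, Cost-effectiveness analyses | yes | yes | yes | yes | yes |
| TiC-P, Table 1 | yes | yes | no | no | yes |
| EQ-5D-5L, Table 1 | yes | no | yes | yes | yes |

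Both Table 1 rows fill all nine columns without a shift. Table 1 has separate columns for B and T1, but the wording in Procedure lets T1 count as baseline, so no conflict is claimed there. The conflict is at 6 and 9 months.

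The TiC-P row is unlikely to be a mere reading error. Its follow-up pattern (3 and 12 months, not 6 or 9) is the same as for the BSI, RRS, OCI-R and BHS. Table 1 therefore shows a coherent shorter battery at 6 and 9 months.

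The EQ-5D-5L row is less certain. It is the only instrument with any mark from 3 to 12 months that lacks one at 3 months, and the row above it has a stray mark.

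**2. Share of the 12 months covered by the TiC-P**

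Assumptions: each form covers the *r* months before it, and the T1 form looks back before treatment, so it adds no follow-up coverage. The recall *r* is not in the document, so a range is shown.

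- Table 1 (forms at 3 and 12): coverage = [min(*r*, 3) + min(*r*, 9)] / 12
- Text (forms at 3, 6, 9 and 12): coverage = 4 × min(*r*, 3) / 12

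| Assumed recall | Table 1 | Text |
|---|---|---|
| 1 month | (1 + 1)/12 = 17% | 4/12 = 33% |
| 3 months | (3 + 3)/12 = 50% | 12/12 = 100% |
| 6 months | (3 + 6)/12 = 75% | 12/12 = 100% |
| 9 months | (3 + 9)/12 = 100% | 12/12 = 100% |

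**3. What a missing 3-month EQ-5D-5L does to the QALY difference**

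Let d3 and d6 be the between-group utility differences at 3 and 6 months, with no difference at T1. Use the trapezoidal area; the article does not state a QALY method, so this is an assumption. From T1 to 6 months:

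- with the 3-month point: 0.25 × d3/2 + 0.25 × (d3 + d6)/2 = 0.25 × d3 + 0.125 × d6
- without it: 0.5 × d6/2 = 0.25 × d6
- with minus without: 0.25 × (d3 − d6/2)

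The area from 6 to 12 months is the same either way. Illustrative differences (assumed; the document gives none):

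| Difference at 3/6/9/12 months | With 3 months | Without | Without minus with |
|---|---|---|---|
| 0.05/0.10/0.10/0.10 (linear to 6) | 0.0750 | 0.0750 | 0 |
| 0.10/0.10/0.10/0.10 (early, sustained) | 0.0875 | 0.0750 | −0.0125 |
| 0.10/0.05/0.05/0.05 (early, halved) | 0.05625 | 0.0375 | −0.01875 |
| 0.10/0/0/0 (early, lost) | 0.0250 | 0 | −0.0250 |
| 0/0.10/0.10/0.10 (delayed) | 0.0625 | 0.0750 | +0.0125 |

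The error can be nil, negative or positive.

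**The case against.** The strongest defence is that this is a condensed article, and the full protocol and the data-capture schedule are not shown. If the five-point schedule in the text is the one in use, costs are collected every three months and only a table error remains. That stands: the article does not reveal which schedule is live, nor which of the two places is wrong.

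The defence also holds on the EQ-5D-5L. No text gives it a schedule, so the empty 3-month cell contradicts nothing, and the stray mark above makes the row doubtful. QALYs can be calculated from T1, 6, 9 and 12 months. The sample size section expects its effect at 3 months on suicidal intrusions, which says nothing about utility at that visit.

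Two stronger readings are tempting. A reader might infer that the 12-month costs and QALYs would be wrong. The document does not support that: costs are incomplete only if Table 1 is followed and recall is shorter than nine months, and QALYs are biased only if the utility difference is not linear from T1 to 6 months, in a direction that cannot be known in advance. A reader might also infer that the Cost-effectiveness analyses section sets EQ-5D-5L visits that Table 1 fails to honour. It does not.

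Finally, the economic evaluation is a later aim, and the article itself describes what the EQ-5D-5L permits in modest terms. That lowers the severity but does not remove the TiC-P contradiction.

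**Conclusion.** The TiC-P schedule contradicts itself at 6 and 9 months. If Table 1 governs, the part of the 12 months left uncovered is 83% with 1-month recall (67% under the text), 50% with 3-month recall, 25% with 6-month recall and none with 9-month recall; under the text it is none from 3-month recall upwards. These figures rest on an assumed recall period and on each form covering only the time just before it.

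The missing 3-month EQ-5D-5L mark is a secondary point to be checked, not a contradiction. If it is real, the incremental QALY shifts by 0.25 × (d3 − d6/2) in size, with either sign possible, and cost and utility are observed together only at T1 and 12 months.

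Severity is moderate. The point bears on the economic evaluation only; the primary outcome, the randomization, the sample size and the efficacy analyses are untouched.

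**What to change.** 1. Check the live data-capture schedule for the TiC-P, then correct whichever of Table 1 and the Cost-effectiveness analyses section does not match what is intended and collected.
2. If the TiC-P is not being collected at 6 and 9 months, add it to the online assessments that already take place then, with recall set to the interval since the previous form. State that recall period.
3. Check the EQ-5D-5L row, including the stray mark on the heading row above it, against the original table. If 3 months is truly absent, add the EQ-5D-5L there so that utilities line up with costs.
4. If some participants have already passed these visits without the forms, say in the economic analysis how the uncovered months are filled, and vary that assumption.

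The cost is slightly more questionnaire burden at up to three existing online assessments and a small amendment. If the live schedule already follows the text for the TiC-P and includes the EQ-5D-5L at 3 months, the only cost is correcting the table.

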### Data management

The proceedings of data security and storage are established in a data management plan. This plan was written according to the guidelines of the funding agent ZonMw. For detailed information about this plan, please contact the first author.

## Discussion

We presented a study protocol to examine the effectiveness and cost-effectiveness of an EMDT intervention added to regular treatment to reduce the frequency and intrusiveness of suicidal intrusions. This study will be the first to investigate experimental effects of treating suicidal intrusions with a dual task method. Given that prior to a suicide attempt, individuals often have passed through various stages including suicidal ideation, and the presence of these uncontrollable, vivid suicidal intrusions could potentially have an influence on the transition from suicidal ideation to actual suicidal behaviour. The EMDT add-on intervention, if proven effective, may therefore be an innovative way to directly reduce the frequency and burden of suicidal imagery [52]. We hope that our study will pave the way for larger studies to evaluate the effectiveness of EMDT on prevention of transition from suicidal ideation to suicidal behavior and on reducing the risk for suicidal behaviour.

## Study status

This is an ongoing study, and the investigators are currently collecting data. Thus far, we have recruited seven mental health institutions that are willing to participate. Each mental health institution has at least one team/department in which EMDT therapists are trained and patients screened for potential inclusion.

## Abbreviations

BDI-II: Beck Depression Inventory
BFT: Breathing Focus Task
BSSI: Beck Scale for Suicidal Ideation
CTQ-SF: Childhood trauma questionnaire – short form
DSMB: Data safety monitoring board
DSM-IV: Diagnostic and statistical manual of mental disorders – 4th edition
EMDR: Eye movement and desensitization reprocessing
EMDT: Eye Movement Dual Task
LDS: Latent difference scores
M.I.N.I.: Mini international neuropsychiatric interview
NTR: Netherlands Trial Register
OCI-R: Obsessive compulsive inventory – short version
PIT: Prospective Imagery Task
PTSD: Posttraumatic stress disorder
QALYs: Quality-adjusted-life-years
RCT: Randomised controlled trial
RIQ: Response to Intrusions Questionnaire
RRS: Ruminative Response Scale
SIDAS: Suicidal Ideation Attributes Scale
SINAS: Suicidal Intrusions Attributes Scale
SUDS: Subjective Units of Distress Scale
TAU: Treatment as Usual
TiC-P: Trimbos/iMTA questionnaire for Costs associated with Psychiatric Illness
